## Abstract

**Background:**

Hospital readmissions remain highly prevalent despite being the target of policies and financial penalties. Evidence comparing the effectiveness and costs of interventions to reduce readmissions is lacking, leaving healthcare systems with little guidance on how to improve quality and avoid costly penalties. Effective interventions likely need to bridge inpatient and outpatient settings, incorporate information technology, and use dedicated providers. Such complex innovations will require rigorous evaluation. The framework of quality improvement research provides an approach that both improves care locally and contributes to closing the current knowledge gaps for readmissions. In this trial, we will study a comprehensive intervention that incorporates these recommendations into an integrated practice unit, called *transition services*, with an aim of reducing 30-day readmission rates.

**Methods/design:**

We describe a nonblinded, pragmatic, controlled trial with two parallel groups comprising an evaluation of the effect of referral to a provider-led integrated practice unit, inclusive of comprehensive multidisciplinary care, dedicated paramedicine providers, and virtual visits, on 30-day readmission rates for high-risk hospitalized patients. An automated risk-scoring system will randomly generate referrals to either transition services or usual care for 1520 hospitalized patients who score as high-risk for readmission. Transition services will then engage with patients in the hospital setting using a patient navigator and provide bridging outpatient services for the 30 days following discharge. All outcome data are retrieved electronically from administrative medical records. After reapplication of inclusion and exclusion criteria at the time of hospital discharge, analyses will follow the intention-to-treat principle such that patients will be analyzed on the basis of the referral group to which they were initially randomized.

**Discussion:**

The hospital transition program under study is complex and integrates the latest recommendations for readmission reduction strategies. As healthcare systems innovate to address readmissions through such complex interventions, there is significant benefit for stakeholders to have a clear understanding of the potential reach, cost, and real-world effectiveness. The pragmatic methods described here provide a template for conducting quality improvement research that fits seamlessly into existing care delivery and improvement efforts, leading to better-informed strategic decisions and the investments necessary to transform care and value for patients.

**Trial registration:**

ClinicalTrials.gov, NCT02763202. Registered 3 March 2016 (retrospectively registered).

**Electronic supplementary material:**

The online version of this article (doi:10.1186/s13063-016-1725-2) contains supplementary material, which is available to authorized users.

## Background

Hospital readmissions are highly prevalent, costly, and associated with poor outcomes [1]. As a result, readmission reduction strategies have been an early target of policy changes and related financial penalties designed to drive quality improvement [1–5]. Beginning in 2012, the Affordable Care Act established a Hospital Readmissions Reduction Program (HRRP) authorizing Medicare to decrease payments to hospitals with excess readmission rates (https://www.medicare.gov/hospitalcompare/readmission-reduction-program.html). A recent analysis showed that, compared with the year 2007 readmission rates, the 2015 readmission rates indeed declined by an average of 2% for Medicare beneficiaries but still remain at approximately 18% for patients with conditions targeted by HRRP (myocardial infarction, pneumonia, and heart failure) [2].

For hospitals seeking guidance on improving readmissions and avoiding financial penalties, high-quality evidence comparing the effectiveness of interventions and related costs is limited and conflicting [3]. Authors of reviews have found no consistent evidence that single interventions produce significant reductions in readmission rates; however, the evidence appears promising for multifaceted interventions bridging the pre- and postdischarge periods [6, 7]. Despite these findings, the most recent large, randomized trial of a postdischarge virtual ward in Canada showed no statistically significant effect on readmission and death [8]. Given the uncertainty of effectiveness and the considerable associated costs, the next generation of multifaceted interventions should be evaluated through rigorous, pragmatic evaluations that clearly identify target populations, cost, and specific implementation factors to optimize generalizability and inform future directions [3, 9–11].

Current evidence suggests this next generation of hospital transition interventions should use analytics to focus on the patients at highest risk for a readmission while incorporating the following: (a) integration of information technology, (b) home-based interventions, (c) new types of transitional care personnel, (d) dedicated transition personnel, and (e) interventions spanning both inpatient and outpatient delivery settings [10]. Our local healthcare system adopted these recommendations into its efforts to improve readmissions by developing a comprehensive program called *transition services*. This program is based on the integrated practice unit (IPU) model that includes physician-led, team-based, integrated services focused on a specific segment of the population [12].

To properly evaluate this transition services program, we designed a randomized quality improvement trial, titled “Aiming to Improve Readmissions Through InteGrated Hospital Transitions” (AIRTIGHT), in which pragmatic methods are used to match the trial design to how the results will be used [13]. This quality improvement research approach is explicitly designed to both improve care locally and contribute to general scientific knowledge [14]. By incorporating the rigor of research methodologies such as randomization, quality improvement research seeks to generate valid and generalizable information that will guide the continuous process of improving care delivery [11, 15]. Similarly, pragmatic trials are designed to determine the effects of an intervention in the “real-world” setting, thus generating results with broad applicability [13, 16]. The Pragmatic-Explanatory Continuum Indicator Summary 2 (PRECIS-2) tool provides a framework for guiding pragmatic trial design to optimize applicability and can be applied to the design of quality improvement research studies [13]. PRECIS-2 assumes that trials have two study arms with unchanged usual care serving as the comparator and contains nine domains representing the applicability of the trial’s eventual results to real healthcare settings. This paper outlines the AIRTIGHT study protocol following both the Standard Protocol Items: Recommendations for Interventional Trials (SPIRIT) guidelines for intervention trials and the PRECIS-2 criteria for pragmatic trials [13, 17]. (The SPIRIT checklist and figure are included as Additional files 1 and 2.)

## Methods/design

### Overview

AIRTIGHT is a nonblinded, pragmatic, controlled trial with two parallel groups in which we are evaluating the effect of referral to a provider-led IPU, inclusive of comprehensive multidisciplinary care and virtual visits, on 30-day readmission rates for high-risk hospitalized patients (Fig. 1). The primary outcome of 30-day, all-cause, any-site readmission will be retrieved electronically from administrative medical record data. Secondary outcomes will all be retrieved in a similar fashion and include 30-day single-site readmission, emergency department use, 60- and 90-day readmissions, length of stay on index admission and readmission, and cost. To provide an understanding of implementation factors, the RE-AIM (Reach, Effectiveness, Adoption, Implementation, Maintenance) framework is incorporated into the study design [18]. The trial is pragmatic across all nine PRECIS-2 domains (Fig. 2). In keeping with this pragmatic framework, the research team has no contact with participants during any aspect of the evaluation. Randomization, patient tracking, and outcomes are all conducted electronically. The AIRTIGHT trial is registered with ClinicalTrials.gov (NCT02763202).

**Fig. 1 Fig1:**
[figure not shown]
Study design and patient flow

**Fig. 2 Fig2:**
[figure not shown]
Pragmatic-Explanatory Continuum Indicator Summary 2 (PRECIS-2) tool. This framework contains nine domains representing the applicability of the trial’s eventual results to real-world healthcare settings

### Study setting

The transition services program will be evaluated in patients under the care of a hospitalist at a tertiary hospital and a smaller satellite hospital, both located within a large integrated healthcare system in Charlotte, NC, USA.

### Eligibility

Patients are eligible for referral if they are over the age of 18 years, are seen by a hospitalist, and have been categorized as an inpatient and as high-risk for readmission, defined as a risk score probability during the first 72 h of admission that is associated with a readmission rate greater than 20%. Patients are excluded if they have a primary residence more than 150 miles from the hospital; are admitted from or discharged to locations such as hospice, skilled nursing facility (SNF), or jail; leave the hospital against medical advice; have an acute psychiatric illness; have been referred as part of the AIRTIGHT evaluation in the previous 90 days; have attended a similar heart failure transitions clinic at discharge; or are being actively care managed for a cancer diagnosis or sickle cell disease. These latter groups have existing, robust care management services in place. Transition services was specifically designed to support the unique needs of patients being discharged to home; consequently, SNF patients were excluded, despite this being a group at high risk for readmission. Also, because the intervention is designed to begin during a patient’s hospital stay, the initial referrals occur early in the course of the hospitalization. However, because we expect changes in some patients’ criteria during the ensuing hospitalization course, the inclusion and exclusion criteria are applied again at discharge (Fig. 1, “Eligible at discharge” bubble).

### Risk score

The readmission risk model used is a neural network. It is built from a final set of 71 variables after the assessment of several thousand variables consisting of demographic, clinical, and use data. The model was built using retrospective information but is applied in a nearly real-time setting during a patient’s inpatient admission. Model performance was determined using a training dataset (70%) as well as a testing dataset (30%), as is typical in predictive model development. Operationally, scoring data for the model are sourced from a patient’s billing history (at the time of admission) as well as using clinical data updated throughout the hospital stay. Examples of information leveraged in the model include variables such as albumin, ammonia, body mass index, fall risk score, inability to verbalize needs, insurance type, living situation, oxygen flow rate, and pain intensity.

Every 1–4 h, a patient’s readmission risk is assessed via the model, and a risk score between 0 and 1 is calculated. This value is then attributed to one of four segments that convey increasing risk of readmission (low, moderate, high, or very high). Outside this study, clinicians use this risk information to assist in discharge planning.

### Randomization and blinding

A referral list is generated each weekday morning by randomly selecting eligible patients during their initial 72 h of admission. A six-person block randomization scheme was used so that, at any point, there are three patients assigned to usual care and three patients assigned to the transition services program. SAS software (SAS Institute, Cary, NC, USA) was used to create this 1:1 allocation, with future allocations concealed from the clinical team [19]. The total referrals are constrained to no more than 30 patients per day, but the total may be adjusted downward on the basis of daily estimates of the transition services’ capacity. Given the nature of the intervention, it is not possible to blind patients or clinicians. For the interim and final outcome analyses, a study statistician and Data and Safety Monitoring Board (DSMB) are not blinded to treatment assignment.

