### Data collection

Each weekday morning, a list of eligible patients in both arms of the study is generated and stored in an SAS dataset. Patients randomized to referral to the transition services program have their information exported to an Excel file (Microsoft, Redmond, WA, USA) for use by the nurse patient navigator. It is within this file that the enrollment status is tracked by the nurse patient navigator. A patient’s choice to decline services through the transition services program is also tracked within this file. The day following list generation, enrollment status is incorporated into the SAS dataset.

Patient data such as demographics and information associated with their hospital encounters, emergency department encounters, and charges will be pulled from tables within the healthcare system’s enterprise data warehouse. Dashboards displaying patient demographics, appointment descriptions (i.e., arrived, no show, canceled visit), enrollment rates, and no-show rates are presented to the clinical teams in Tableau files [23].

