### Analysis

All analyses will follow intention-to-treat principle such that patients will be analyzed on the basis of the group to which they were initially randomized, but after reapplication of inclusion and exclusion criteria at the time of hospital discharge (Fig. 1, “Eligible at discharge” bubble). Baseline comparisons of the two groups will be made using univariate analyses such as the *t* test and chi-square test. The primary outcome, readmission in 30 days, will be compared between the two groups of patients who are eligible at discharge, using logistic regression. Results will be presented with ORs and 95% CIs. In addition to the intention-to-treat analysis, we will perform a per-protocol analysis to evaluate the patients who are eligible at discharge and participate in the transition services program compared with usual care patients who are eligible at discharge. For all outcomes, we assume that if there are no visits in the electronic medical record, the value for having a visit is null; therefore, there will be no missing data for the primary or secondary outcome measures.

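### A study statistician is left unblinded for the final analysis, without a reason, although the analysis set is fixed after randomization; the flags and model code should be locked before the arm is merged

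*Protocol article*

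**What the plan says.** The protocol article first gives a reason for the open design: "Given the nature of the intervention, it is not possible to blind patients or clinicians" (Randomization and blinding). The next sentence extends unblinding to the analysis, interim and final alike: "For the interim and final outcome analyses, a study statistician and Data and Safety Monitoring Board (DSMB) are not blinded to treatment assignment". No reason is attached to the final analysis.

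The set of patients to be compared is settled after randomization. Under Eligibility, "the inclusion and exclusion criteria are applied again at discharge". Under Analysis, patients are kept in their randomized group, "but after reapplication of inclusion and exclusion criteria at the time of hospital discharge", and the primary comparison covers those still eligible at that point.

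Some of the criteria are open in their wording: "are admitted from or discharged to locations such as hospice, skilled nursing facility (SNF), or jail", "are being actively care managed for a cancer diagnosis or sickle cell disease", and acute psychiatric illness. Another depends on care around discharge: "have attended a similar heart failure transitions clinic at discharge". Others are plainly administrative, such as age, distance of residence and a previous referral within 90 days.

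Under Data collection, patients referred to transition services are exported to a spreadsheet for the nurse navigator. "It is within this file that the enrollment status is tracked by the nurse patient navigator". Refusals are recorded there too. Enrollment status then goes into the SAS dataset the day after the list is generated. The article describes no such file for usual care.

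**The concern.** The nature of the intervention explains why patients and clinicians know the arm. It does not explain why the person working on warehouse data must know it when the final analysis is prepared. The interim efficacy and futility analysis does need someone unblinded; the final analysis does not until the data are locked.

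Where every randomized patient is counted, an unblinded analyst has little say over who enters the comparison. Here, membership of the analysis set is itself a classification made after randomization. If open terms are turned into flags, or code is revised, while the arm is visible, inclusion could drift in one direction without anyone intending it. Patients and clinicians are already unblinded, so masked derivation of the flags is one of the few protections against bias still available.

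**Working it through.** **1. The plan's own figure.** Inputs from Sample size: 20% versus 14%, α = 0.05 (taken as two-sided), 80% power, chi-square test.

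n per arm = [1.960 × √(2 × 0.17 × 0.83) + 0.842 × √(0.20 × 0.80 + 0.14 × 0.86)]² / 0.06² = 614.1, rounded up to 615, so 1230 in total. This matches the article. The increase for 10% non-participation is 1230 / 0.9² = 1518.5, in line with the stated 1520 (760 per arm). The diluted intervention rate is 0.9 × 14% + 0.1 × 20% = 14.6%, and power at 760 per arm is then 79.5%. Masking the analyst changes none of these numbers.

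**2. How many exclusions change the verdict.** Assumptions: 760 per arm in the analysis set, usual care fixed at 152/760 (20%), Pearson chi-square without continuity correction, two-sided 0.05. With cells a, b (readmitted, not readmitted) in one arm, c, d in the other, and N = a + b + c + d:

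χ² = N(ad − bc)² / [(a + b)(c + d)(a + c)(b + d)]

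With no exclusions the boundary lies between 122/760 (p = 0.045) and 123/760 (p = 0.053) in the intervention arm.

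A worked case: 125/760 gives χ² = 3.22, p = 0.073. Removing two readmitted intervention patients gives 123/758, p = 0.056. Removing three gives 122/757, χ² = 3.87, p = 0.049.

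Removing readmitted intervention patients one at a time until p < 0.05:

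| Intervention arm at start | p at start | Removals needed | Share of 1520 |
|---|---|---|---|
| 123/760 | 0.053 | 1 | 0.07% |
| 127/760 | 0.098 | 6 | 0.4% |
| 131/760 | 0.17 | 11 | 0.7% |
| 139/760 | 0.40 | 20 | 1.3% |
| 151/760 | 0.95 | 35 | 2.3% |

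In the other direction, the planned diluted effect is 111/760 against 152/760 (p = 0.005). Removing 15 readmitted usual-care patients leaves 137/745 and p = 0.048; the sixteenth leaves 136/744 and p = 0.054. So 16 are needed to lose significance.

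With 615 or 500 per arm, starting points close to the boundary again need 1 to 6 removals.

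**3. What the article leaves open.** It does not give the number of patients expected to be affected by the discharge check, nor how many of those cases would need judgement. The table therefore shows how sensitive the verdict is to one-sided exclusions. It does not show how many will occur.

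**The case against.** A reader might infer that the statistician personally rules on borderline eligibility or codes readmissions by judgement. The document does not say so. The Overview describes randomization, tracking and outcomes as electronic. Outcomes adopts the CMS definition of a nonelective readmission, with observation stays added, and restricts itself to routine-care data so that assessment does not differ between arms. The discharge check may well be a program. The open wording of the criteria may also reflect the condensation of a journal article, with code lists in a fuller document; the absence of those lists is not held against the plan here.

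A reader might also infer that the final analyst will already know the interim results by arm. The article speaks of a study statistician in one section and an unblinded statistician in another, and does not say they are the same person.

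The sensitivity is also selective. Any trial that lands near 0.05 can be tipped by a few patients all removed in the same direction, and the planned effect would withstand 15 such removals. Finally, discharge destination, heart failure clinic attendance and care-management status arise during care by clinicians who know the arm, and masking the analyst does nothing about that.

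All of this stands and limits the point. It does not remove it. Routine data protect how events are recorded; they do not fix when eligibility terms are turned into flags relative to the arm becoming visible. The unblinding at the final analysis is stated outright, so it is a choice the article has made and not a detail it leaves elsewhere.

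**Conclusion.** The point holds as a minor improvement to the design. The article leaves a study statistician unblinded for the final analysis without a reason, in a trial whose primary set is determined after randomization and whose dataset takes in tracking data from one arm only. That is an avoidable exposure. It is not evidence that arm-aware decisions will be made.

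Its size is conditional. If the discharge check were applied with the arm in view, about 1 to 6 one-sided exclusions could turn a result with p between roughly 0.05 and 0.10 significant. A result further from the threshold would need about 11 to 35, and overturning the planned diluted effect would need 16. These counts assume 20% readmission in usual care, 760 analysed per arm, and exclusions that are all readmitted patients from one arm.

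**What to change.** Restrict the unblinded role to the interim report to the DSMB. For the final analysis:

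1. Derive the eligible-at-discharge flag and the outcome flags by a programmed rule, on a dataset that holds neither the true arm nor the navigator file.
2. Finalise the primary model code on that same dataset.
3. Lock the flags and the code, and only then merge the allocation.
4. Add the participation variables for the per-protocol analysis after the lock, since they reveal the arm.

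The cost is a sentence or two of text and a short lock step before results are available. It takes no patients, no power and no further data. Because the arm is absent when the flags are derived by rule, it need not take extra staff either.

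The text should say what this covers: arm-aware decisions in the analysis. It does not address the influence of unblinded clinicians on a patient's status at discharge.

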### Trial intervention and control

Control patients will receive usual care. Standard discharge care at both hospitals includes recommendations for follow-up appointments with a patient’s primary care physician, discharge summaries sent to primary care physicians, the arrangement of home health services based on each patient’s needs, and other outreach interventions such as follow-up care management phone calls.

In addition to usual care, patients referred to the intervention group are contacted during their hospital stay by a registered nurse patient navigator, invited to participate in the transition services program, and then followed for the remainder of their hospital stay. For 30 days following discharge, patients have access to the transition services program, which, in addition to a free-standing clinic, includes the following: (a) as-needed access to transition-dedicated internal medicine, pharmacist, paramedicine, behavioral health, and care management providers; (b) hospital follow-up evaluation with a medical provider, either virtually in the patient’s home facilitated by a paramedicine provider or in the transition clinic; (c) medication reconciliation by a pharmacist; (d) at least weekly contact with the care management team; (e) 24/7 phone support, 24/7 paramedicine visit availability, and same-day clinic scheduling; and (f) coordinated transition to the next appropriate care location after 30 days (Table 1). The intensity of the care provided is not prescribed but rather dictated by the care team and patient. At a minimum to qualify as having participated, patients will have an in-person or virtual visit with the transition services medical provider. Patients or their insurance providers are charged only for services that are billable under usual care, whereas all other services are provided by the healthcare system as part of care management.

**Table 1 Tab1:** Transition services program intervention components

Transition services components	Transition recommendations [10] and drivers of readmissions addressed
Referral to transition services program and introduction by patient navigator while patient is still hospitalized	• Dedicated transition personnel • Spanning inpatient and outpatient • Engagement • Discharge plan confusion
Comprehensive postdischarge evaluation by internal medicine physician	• Dedicated transition personnel • Spanning inpatient and outpatient • Access • Timely follow-up of items outstanding at discharge • Early identification of change in patient status
Postdischarge medication reconciliation by a pharmacist	• Dedicated transition personnel • Medication errors, misunderstanding, adherence
In-home virtual appointments	• Home-based interventions • Integration of IT • Access
24/7 availability of dedicated paramedicine team for in-home visits	• Home-based interventions • New types of transitional care personnel • Dedicated transition personnel • Access • Coordinated service between home and clinic
Multidisciplinary team (internal medicine, pharmacist, paramedicine, behavioral health, and care management providers)	• Dedicated transition personnel • Access to comprehensive follow-up services
Regular care management contact starting with discharge follow-up call and weekly thereafter	• Dedicated transition personnel • Coordinated care • Engagement
Real-time population health dashboards for clinic staff	• Integration of IT
Coordinated transition to the next appropriate care location after 30 days	• Spanning inpatient and outpatient • Coordinated care • Intraprovider communication

*IT* Information technology

